## Abstract

**Background:**

Elderly patients are particularly vulnerable to adverse drug reactions, especially if they are affected by additional risk factors such as multimorbidity, polypharmacy, impaired renal function and intake of drugs with high risk potential. Apart from these clinical parameters, drug safety and efficacy can be influenced by pharmacogenetic factors. Evidence-based recommendations concerning drug-gene-combinations have been issued by international consortia and in drug labels. However, clinical benefit of providing information on individual patient factors in a comprehensive risk assessment aiming to reduce the occurrence and severity of adverse drug reactions is not evident. Purpose of this randomized controlled trial is to compare the effect of a concise individual risk information leaflet with standard information on risk factors for side effects.

**Methods/Design:**

The trial was designed as a prospective, two-arm, randomized, controlled, multicenter, pragmatic study. 960 elderly, multimorbid outpatients in general medicine are included if they take at least one high risk and one other long-term drug (polymedication). As high risk “index drugs” oral anticoagulants and antiplatelets were chosen because of their specific, objectively assessable side effects. Following randomization, test group patients receive an individualized risk assessment leaflet evaluating their personal data concerning bleeding- and thromboembolic-risk-scores, potential drug-drug-interactions, age, renal function and pharmacogenetic factors. Control group patients obtain a standardized leaflet only containing general information on these criteria. Follow-up period is 9 months for each patient. Primary endpoint is the occurrence of a thromboembolic/bleeding event or death. Secondary endpoints are other adverse drug reactions, hospital admissions, specialist referrals and medication changes due to adverse drug reactions, the patients’ adherence to medication regimen as well as health related quality of life, mortality and resulting costs.

**Discussion:**

Despite extensive evidence of risk factors for adverse drug reactions, there are few prospective trial data about an individualized risk assessment including pharmacogenetic information to increase patient safety. By conducting a health economic analysis, we will evaluate if the application of an individualized drug therapy in daily routine is cost-effective.

**Trial registration:**

German Clinical Trials Register: DRKS00006256, date of registration 09/01/15.

## Background

Adverse drug reactions (ADR) represent a major public health issue not only due to the morbidity and mortality but also due to the extra costs they cause. About 5–10 % of all hospital admissions are estimated to be ADR-associated, 2–6 % of them are fatal [1–5]. According to analyses of ADR case reports, approximately 40–60 % of all ADR are considered to be preventable [2, 3, 5, 6]. It has been reported that the incidence of ADR increases with age [1, 4–6]. This may be explained by age-related changes in pharmacokinetics, such as increased drug concentrations due to decreased total body water and impaired renal function [7, 8]. Additionally, the prevalence of multimorbidity and polypharmacy is very high in the elderly [9, 10]. In a recent systematic review on ADR in the elderly, these two parameters have been mentioned as significant risk factors for ADR, alongside female sex, impaired renal function, drug-drug-interactions and drugs with narrow therapeutic index, e. g. anticoagulants [11].

Pharmacogenetic factors are known to influence dosing and drug efficacy in patients [12]. For example, clopidogrel effectiveness depends on its transformation into an active metabolite by the genetically variable enzyme cytochrome P 450 2C19 (CYP2C19). Reduced enzyme function has been shown to be significantly associated with decreased platelet inhibition [13–15]. For vitamin K antagonists, cytochrome P 450 2C9 (CYP2C9) is the main drug metabolizing enzyme, and vitamin K epoxide reductase (VKORC1) represents the drugs’ target. They have been shown to significantly influence dosing requirements and anticoagulation stability [16–18]. Evidence-based recommendations for these drugs according to the respective genotypes have been published by the Royal Dutch Pharmacists Association - Pharmacogenetics Working Group [19] and the Clinical Pharmacogenetics Implementation Consortium (CPIC) [20]. The European Medicines Agency (EMA) and the U.S. Food and Drug Administration (FDA) have included pharmacogenetic information for clopidogrel in the drug labels, the FDA also for the vitamin k antagonist warfarin [21, 22].

Another measure to increase patient safety is the use of computerized clinical decision support systems. They have been shown to be a cost-effective possibility to reduce preventable ADR and medication errors in inpatient and ambulatory care [23–26]. Furthermore, some randomized controlled trials investigating the effect of a comprehensive medication review in elderly populations have suggested a reduction of medication-related hospital admissions, but the studies were underpowered and the results were not statistically significant [27, 28]. Therefore, a randomized controlled trial with a large cohort of patients at particularly high risk for ADR is needed for further investigation.

The aim of this study is to test if individualization of drug therapy based on the most important categories of relevant known ADR risk factors may improve safety and individual efficacy of drug therapy if the doctor and the patient are getting this information in a timely and easy-to-understand format. We focus our study on a collective of elderly, multimorbid, polymedicated ADR-high risk patients. As antithrombotics range among the most frequently ADR-associated drugs leading to hospitalizations in the elderly [29, 30] and have high potential for particularly severe ADR [31, 32], these drugs were determined as index medication for the study.

## Methods/Design

### Study aim

The aim of the study is to evaluate the effect of an individualized comprehensive risk assessment and information leaflet regarding medication compared to a standardized one on adverse drug reactions in an elderly high risk population.

### Design

The IDrug-study is a prospective, multicenter, two-arm, randomized, controlled, pragmatic trial. Eligible patients are randomized to either test or control group. Control group patients receive a standardized information leaflet about risk factors for ADR. An individualized leaflet containing the same general information plus an additional individualized risk assessment is handed out to test group patients. In the following passages, the study design will be described in detail.

### Study endpoints

Primary endpoint is the occurrence of a thromboembolic or bleeding event or death within a 9 months study period. Secondary endpoints are the occurrence of other ADR, the number of hospital admissions due to ADR, the number of specialist referrals due to ADR, the number of medication changes, the patients’ adherence to the medication regimen, time to death, health-related quality of life, costs of medication and of additional general practitioner (GP) consultations and hospital treatments as well as a cost-benefit analysis.

### Inclusion and exclusion criteria

Patients are eligible if they are at least 60 years old, have more than one chronic disease and take two or more prescription drugs. They have to be on long-term treatment with oral anticoagulants (phenprocoumon, warfarin, dabigatran, apixaban, rivaroxaban) or antiplatelets (clopidogrel, prasugrel, ticagrelor, ticlopidin) as high risk index medication. Furthermore, they must be physically and mentally able to give written consent to participate in the study. Patients will be excluded if they are unable to give consent or unable to fill in the required questionnaires (SF-36 for health-related quality of life [33], Morisky score for adherence to medication regimen [34] and social state).

### Sample size

Sample size calculation was based on the primary endpoint and its primary analysis. Preceding studies reported incidence rates ranging from 8 to 10.6 % for thromboembolic and bleeding events in a population of elderly polymedicated patients on oral anticoagulants [32, 35]. Thus, for sample size calculation, we assumed an incidence rate of 10 % in the control group, which we assumed to be reduced by half as a result of the individualized risk assessment (i.e. to 5 %). To detect this anticipated difference with a power of 80 % using the Cochran-Mantel-Haenszel test (assuming equal effects in all strata), a sample size of 435 patients per arm is required. Assuming a dropout rate of 10 % about 960 patients need to be included in the study.

### Recruitment

The study is conducted in the area of Bonn, Cologne and the Rhine-Sieg-district, Germany. 40–80 GP-practices situated in this area participate in the study. After being instructed by the Institute of General Practice and Family Medicine Bonn, the general practitioners create a list of eligible patients. They name the number of patients to the institute and in return obtain in a first step a random selection of 10 patients to be asked by the GP to participate in the study. This random selection is performed using prefabricated lists provided by the Department of Biostatistics of the Federal Institute for Drugs and Medical Devices Bonn to avoid selection bias. Overall each GP-practice is planned to enroll 12–24 patients. The workflow of the IDrug study is illustrated in Fig. 1.

**Fig. 1 Fig1:**
[figure not shown]
Workflow IDrug study. Each GP provides a list of all patients meeting the inclusion criteria. The order of patient enrollment is random. Following randomization to a study arm, the patients receive either a standardized or an individualized risk assessment leaflet and are followed up for 9 months. 870 patients will be required, and considering an estimated dropout rate of 10 % 960 patients need to be included. At the end of the study, both groups will be compared regarding primary and secondary endpoints

### Patient information and inclusion

Written informed consent is obtained by the general practitioner. After enrollment, a blood sample is taken and sent to the accredited Institute of Clinical Chemistry and Clinical Pharmacology of the University of Bonn for genotyping (*CYP2C9, CYP2C19* and *VKORC1*). The patient’s medical history is documented on paper-based Case Report Forms (CRF). The collected data include the patient’s demographic data, such as age, gender, weight, height, blood test results (creatinine, thrombocytes, hemoglobin and liver enzymes), alcohol consumption, smoking state, anticoagulation/antiplatelet therapy regimen, medication and diagnoses. Additionally, the HAS-BLED-Score [36] for bleeding risk (hypertension, abnormal renal/liver function, stroke, bleeding history or predisposition, labile internationalized normalized ratio, elderly (>65 years), drugs/alcohol concomitantly) and the CHA2DS2-VASc-Score [37] for thromboembolic risk (congestive heart failure, hypertension, age, diabetes, stroke, vascular disease, age, sex category) are recorded. Once completely filled in, the CRF is faxed to the Federal Institute for Drugs and Medical Devices Bonn for randomization and risk assessment.

### Randomization

Randomization is performed upon receipt of the CRF and is stratified by GP-practice and gender to account for potential influence of GP and gender and to ensure balanced groups within each stratum. Randomization lists are provided by the Biostatistics Unit of the Federal Institute for Drugs and Medical Devices Bonn. According to the allocated study-arm, either a standardized or an individualized risk assessment leaflet is written and sent out to the GP in duplicate, as one copy will be handed out to the patient.

### Risk assessment

Both risk assessment leaflets contain general information on risk factors for adverse drug reactions. However, the individualized leaflet also includes an additional personalized risk evaluation which takes the patients clinical data into account. For test group patients, their individual HAS-BLED- and CHA2DS2-VASc-Scores are calculated. The current medication is checked for potential drug-drug-interactions and it is checked whether dose adjustments related to the patients’ kidney function would apply, using two independent validated evidence-based clinical decision support systems, AiDKlinik® [38] and the ABDA database [39]. Furthermore, the patients’ genetic profiles for *CYP2C9*, *CYP2C19* and *VKORC1* are matched with their medication to check for potential drug-gene-interactions according to their genotypes. References are the guidelines published by the Royal Dutch Pharmacists Association - Pharmacogenetics Working Group [19] and the Clinical Pharmacogenetics Implementation Consortium (CPIC) [20]. The standardized leaflet, however, only contains general information about these risk factors for adverse drug reactions.

The leaflets have a short and clearly arranged design in order to be implementable in everyday practice. They only contain clinically relevant information. Additionally, they are written in a generally understandable manner, so that they can be read easily by doctors as well as patients. A scheme of the risk assessment leaflets is displayed in Fig. 2.

**Fig. 2 Fig2:**
[figure not shown]
Scheme of the risk assessments. Both versions of risk assessment leaflets contain general information on the following risk factors for ADR: HAS-BLED- and CHA2DS2-VASc-Score, drug-drug-interactions, age, renal function and pharmacogenetic factors. The individualized risk assessments additionally include a personalized evaluation of the patient’s personal data

### Follow-up and blinding

Follow-up time is 9 months for each patient. Overall, 4 visits are scheduled at intervals of 3 months. The study starts at visit 1 when the patient receives the risk assessment leaflet. During this visit, the general practitioner hands out the leaflet and explains its contents to the patient. It is at the discretion of the GP in which way and to what extent he uses the provided information for further treatment, no specifications are made. Patients are considered to be blinded to group assignment, since group assignment is not actively communicated at any time and both risk assessment leaflets have a very similar layout.

During each visit, the following information is documented in the CRF: reason for GP-consultation, vital signs, ECOG score for the patient’s physical condition [40], adverse events (bleeding events, thromboembolic events and others), number of GP-consultations in the meantime, specialist referrals, hospital admissions, sick leaves, remedies and aids and other procedures (e. g. emergency department visits, rehabilitation etc.). Data about anticoagulation/antiplatelet therapy regimen, medication and diagnoses are updated during each visit. Additionally, patients are asked to fill in questionnaires about their health related quality of life (SF-36 [33], filled in at each visit), their adherence to the medication regimen [34] (filled in at the beginning and end of the study) and their social state (filled in once at the beginning of the study).

### Data management and monitoring

The patients’ data is documented on paper-based Case Report Forms by the general practitioners, the practice staff and staff of the Institute of General Practice and Family Medicine Bonn. It is transferred to a GCP conform electronic database by the data management of the Federal Institute for Drugs and Medical Devices Bonn. To guarantee data quality, double data entry is performed. Queries are documented in an electronic database and processed during monitoring visits. For each practice, three of these visits are scheduled. The first one takes place after inclusion of 1 to 3 patients, the second one after inclusion of 10 to 15 patients and the third one when the practice finishes the study. Furthermore, practices are monitored via telephone and additional interim visits regularly. Monitoring is performed by the Study Center of the Institute of Clinical Chemistry and Clinical Pharmacology, University of Bonn.

### Dropout criteria

Study participation is terminated if the patient withdraws consent or if continuous data collection cannot be guaranteed (e. g. if the patient changes the GP or is absent for a long time). Discontinuation of anticoagulant/antiplatelet therapy after start of the study and receipt of the risk assessment leaflet (visit 1) does not lead to exclusion.

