### Statistical analysis

#### Primary endpoint

The proportion of patients with an event (i. e. thromboembolic or bleeding event or death) will be compared between the two study arms using the Cochran-Mantel-Haenszel-Test stratified by gender and medical practice. Following the intention-to-treat principle, all randomized patients will be analyzed according to their randomized allocation. Dropouts will be counted as treatment failure in primary analysis. Risk reduction is estimated by the Mantel-Haenszel estimator of the common relative risk with the corresponding 95 % confidence interval. Additional sensitivity analyses will be performed, which include evaluation of different covariate structures.

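### Patients who change GP or are long absent are dropped without withdrawing consent and then counted as failures, so obtainable event-free outcomes enter the primary endpoint as events

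*Protocol article*

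**What the plan says.** The section Dropout criteria gives two grounds for ending participation. One is withdrawal of consent. The other is that continuous data collection cannot be assured, illustrated by "if the patient changes the GP or is absent for a long time". The second ground covers patients who have not withdrawn consent. The same section keeps patients who stop the index drug after visit 1.

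Under Statistical analysis, Primary endpoint, "all randomized patients will be analyzed according to their randomized allocation", and "Dropouts will be counted as treatment failure in primary analysis". The endpoint is whether a thromboembolic event, a bleeding event or death occurred within 9 months.

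Sample size allows for 10 % dropout, about 960 patients in all, but only as lost numbers. The extra failures that the analysis rule creates from those dropouts are not in the calculation.

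**The concern.** The primary endpoint needs each patient's event and vital status over 9 months. It does not need unbroken visits at one practice; only measures taken at the visits, such as the SF-36, do. The termination rule nevertheless stops follow-up on logistical grounds, and the analysis rule fills the gap with a failure. For an event-free patient, an outcome that could have been obtained is replaced by an event that did not happen.

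Two things are at stake.

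- **Dilution.** False events added to both arms pull the relative risk towards 1 and cost power.
- **Bias.** If dropout differs between arms, failure scoring creates a difference of its own. What counts as a long absence is left to judgement, and the Discussion concedes that GPs see both leaflets and may come to recognise the groups.

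**Working it through.** **Inputs from the protocol article**
- Control rate: "we assumed an incidence rate of 10 % in the control group". Test-arm rate: half of that, 5 %.
- Power 80 %, and "a sample size of 435 patients per arm is required" (Sample size).
- Dropout 10 % and about 960 patients, so 480 per arm.
- Alpha is not stated. I assume two-sided 5 %, in line with the planned 95 % confidence interval.

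**Reproducing the plan's figure.** With pooled variance and no continuity correction, p̄ = 0.075:

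n = [1.96·√(2·0.075·0.925) + 0.8416·√(0.10·0.90 + 0.05·0.95)]² / 0.05² = (0.7301 + 0.3121)² / 0.0025 = 434.4, so 435 per arm. This matches. For the total, 870/0.9 = 967 and 870·1.1 = 957, so about 960 is acceptable.

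**Rates once dropouts are failures.** If dropout d is equal in both arms and independent of events, the analysed rate is d + (1 − d)·p. With d = 0.10:
- control: 0.10 + 0.90·0.10 = 19.0 %
- test: 0.10 + 0.90·0.05 = 14.5 %

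In patients per arm, the true events are 48 and 24. Of the 48 dropouts in each arm, 43.2 (control) and 45.6 (test) are event-free but counted as events.

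**Power** = Φ{[|p₁ − p₂| − 1.96·√(2p̄(1 − p̄)/n)] / √[(p₁(1 − p₁) + p₂(1 − p₂))/n]}, n = 480. For 19.0 % v 14.5 %: (0.045 − 1.96·0.02410)/0.02406 = −0.093, so 46 %.

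If a share of the dropouts has its outcome recovered, the remaining d shrinks:

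| Share recovered | Remaining d | Control v test | RR | Power |
|---|---|---|---|---|
| none | 10 % | 19.0 % v 14.5 % | 0.76 | 46 % |
| a quarter | 7.5 % | 16.75 % v 12.1 % | 0.72 | 53 % |
| half | 5 % | 14.5 % v 9.75 % | 0.67 | 62 % |
| three quarters | 2.5 % | 12.25 % v 7.4 % | 0.60 | 72 % |
| all | 0 % | 10 % v 5 % | 0.50 | 84 % |

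**If dropout is event-related.** Suppose a share g of events leads to dropout, total control dropout stays at 10 %, and event-free patients drop out at the same rate q in both arms: q = (0.10 − 0.10g)/0.90.
- g = 30 %: q = 7.8 %; 17.0 % v 12.4 %; power 52 %.
- g = 50 %: q = 5.6 %; 15.0 % v 10.3 %; power 60 %.

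The loss is smaller, because patients who had the event are correctly scored. This depends on equal q. If total dropout were instead 10 % in both arms with g = 30 %, q in the test arm would be (0.10 − 0.015)/0.95 = 8.9 %, the rates 17.0 % v 13.5 %, and power 33 %.

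**If dropout differs by arm (illustration).** With no true effect (10 % in both arms) and dropout of 12 % v 8 %, the analysed rates are 0.12 + 0.88·0.10 = 20.8 % and 0.08 + 0.92·0.10 = 17.2 %. The standard error is 0.0253 and z = 0.036/0.0253 = 1.42, so a nominal 5 % test rejects about 30 % of the time.

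All figures ignore the practice and gender strata.

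**The case against.** **The power loss belongs to the failure rule.** This largely stands. The fall from 84 % to 46 % comes from scoring dropouts as failures. The termination rule only supplies patients to it, so a reader should not charge the whole loss to the dropout criteria, nor count it again in any separate criticism of the failure rule.

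**The recoverable share is unknown.** This stands. The split between consent withdrawal and GP change or absence is not given, and withdrawals cannot be traced. Full recovery is a ceiling.

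**Event-related dropout does less harm.** A reader might infer that the rule removes the patients most likely to have had a stroke or bleed and so hides their events. The article does not say that absences follow events. Where they do, failure is the correct score. The harm falls on event-free patients.

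**No breach of intention-to-treat.** A reader might infer that the dropout rule contradicts the stated analysis. It does not: everyone randomized is kept in the allocated arm. The weakness is in outcome completeness.

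**Earlier events are still captured.** Events are documented at the three-monthly visits, so termination loses only the time after the last contact. True, but an event-free patient is scored as a failure however short that gap.

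**This is a condensed article.** The full protocol may describe tracing after termination, and its absence here is not the finding. The two rules questioned are both stated, and as stated they turn a known or obtainable event-free outcome into an event.

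**Conclusion.** The point holds as a design weakness that should be corrected. Taken together, the termination rule and the failure rule enter event-free patients with obtainable outcomes as events.

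How much of the range from 46 % to 84 % power can be regained depends on the unstated share of recoverable dropouts. A quarter recovered gives 53 % and half gives 62 %. These figures assume two-sided 5 %, 480 per arm, 10 % dropout equal in both arms and independent of events, and the plan's 10 % v 5 %. The loss is smaller if dropout is event-related and event-free patients leave at the same rate in both arms. The bias figure only shows what unequal dropout could do; nothing in the article shows that dropout will be unequal.

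The documents support neither a conflict with intention-to-treat nor attributing the full power loss to the termination rule.

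**What to change.** State that only withdrawal of consent to data collection ends follow-up for the primary endpoint. Patients who change GP or are long absent may miss visits but stay in outcome follow-up. For them, obtain vital status and any bleeding or thromboembolic events up to month 9 from the patient, a relative or the new practice. Use the same procedure in both arms and cover it in the consent form. Score as failures only those whose status remains unknown.

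The section on ethics approval and data protection keeps identifying data at the GP practices, so the original practice must make the contact and pass on pseudonymised results. Practice staff already complete the case report forms.

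The cost is protocol, consent and data-protection wording, plus contacts for fewer than about 96 patients (10 % of 960, less the consent withdrawals). Ascertainment by a single contact will be less detailed than at visits, which matters most for minor bleeding. No extra visits are needed and treatment is unaffected.
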